#### **14.5 Privacy, Confidentiality, and Data Storage**

The Principal Investigator will ensure that subject privacy and confidentiality of the subject's data will be maintained. Research Data Security Plans (RDSPs) will be approved by the appropriate institutional Site Based Research group. To protect privacy, every reasonable effort will be made to prevent undue access to subjects during the course of the study. Prospective participants will be consented in an exam room where it is just the research staff, the patient and his family, if desired. For all future visits, interactions with research staff (study doctor and study coordinators) regarding research activities will take place in a private exam room. All research related interactions with the participant will be conducted by qualified research staff who are directly involved in the conduct of the research study.

To protect confidentiality, subject files in paper format will be stored in secure cabinets under lock and key accessible only by the research staff. Subjects will be identified only by a unique study number and subject initials. Electronic records of subject data will be maintained using dedicated databases: eResearch, REDCap, and Epic Dashboard, which is housed in an encrypted and password-protected (required: please specify storage device, i.e. laptop computer, desktop computer, DCI file server). Access to electronic databases will be limited to study staff. Subject data may be stored temporarily on encrypted and password-protected portable memory devices such as flash drives and external hard drives, but only when absolutely necessary. Data stored on portable memory devices will be de-identified. Subject data will be deleted from the portable memory device at the earliest opportunity. The security and viability of the IT infrastructure will be managed by the DCI and/or Duke Medicine. Upon completion of the study, research records will be archived and handled per DUHS HRPP policy. Subject names or identifiers will not be used in reports, presentations at scientific meetings, or publications in scientific journals.

#### **14.6 Data and Safety Monitoring**

Data and Safety Monitoring will be performed in accordance with the DCI Data and Safety Monitoring Plan. For a more detailed description of the DSMP for this protocol, refer to Section 11 (Sections 11.7 and 11.8 in particular) along with section 12.

#### **14.7 Protocol Amendments**

All protocol amendments must be initiated by the Principal Investigator and approved by the IRB prior to implementation. IRB approval is not required for protocol changes that occur to protect the safety of a subject from an immediate hazard. However, the Principal Investigator must inform the IRB and all other applicable regulatory agencies of such action immediately.

#### **14.8 Records Retention**

The Principal Investigator will maintain study-related records for at least six years after study completion.

## 16 APPENDICES

### Appendix 1: Smoking Related Medical History

#### MEDICAL HISTORY pg. 1

##### Major Medical Conditions

Have you had any of the following conditions?

- |                                                    |                                                                                          |
|----------------------------------------------------|------------------------------------------------------------------------------------------|
|  Yes  No | Uncontrolled high blood pressure (Hypertension) or hypotension with symptoms (<90/60)    |
|  Yes  No | Heart attack OR heart disease diagnosis by coronary angiogram                            |
|  Yes  No | Problems with heart valves such as regurgitation, stenosis, or artificial valve          |
|  Yes  No | Heart rhythm problem such as atrial fibrillation, tachycardia, or pacemaker              |
|  Yes  No | Chest pains related to the heart in the last month                                       |
|  Yes  No | Heart failure                                                                            |
|  Yes  No | Skin problems requiring medication                                                       |
|  Yes  No | Liver cirrhosis (with jaundice or swollen abdomen)                                       |
|  Yes  No | Liver problems other than cirrhosis (e.g. hepatitis, fatty liver)                        |
|  Yes  No | Kidney failure requiring dialysis                                                        |
|  Yes  No | Chronic Kidney Disease not requiring dialysis                                            |
|  Yes  No | Chronic diarrhea due to Irritable Bowel Syndrome, Crohn's Disease, or Inflammatory Bowel |
|  Yes  No | Stomach/Duodenal Ulcer (Gastrointestinal Ulcer)                                          |
|  Yes  No | Chronic Bronchitis (cough every morning)                                                 |
|  Yes  No | Chronic Obstructive Pulmonary Disease (COPD) (Emphysema)                                 |
|  Yes  No | Use of oxygen                                                                            |
|  Yes  No | Asthma                                                                                   |
|  Yes  No | Other chronic lung disorder such as Tuberculosis, Pulmonary Fibrosis, Sarcoid, or other  |
|  Yes  No | Stroke/TIA (mini-stroke)/brain tumor                                                     |
|  Yes  No | Seizure disorder                                                                         |
|  Yes  No | Regular headaches or migraines that occur more than one per week                         |
|  Yes  No | Unexplained fainting spells                                                              |
|  Yes  No | Insomnia requiring medications                                                           |
|  Yes  No | Other neurologic conditions                                                              |
|  Yes  No | Problems giving blood samples                                                            |
|  Yes  No | Blood disorder or Anemia requiring iron                                                  |
|  Yes  No | Rheumatic Disease such as Rheumatoid Arthritis, Fibromyalgia, or other                   |
|  Yes  No | Sinusitis/Seasonal allergies                                                             |
|  Yes  No | Diabetes with uncontrolled blood sugar (>200 more than once/week) or on insulin          |
|  Yes  No | Thyroid disease/condition                                                                |
|  Yes  No | Current cancer or treatment for cancer in the past 6 months                              |
|  Yes  No | Depression/Anxiety/Bipolar disorder/psychiatric hospitalization in the past 3 months     |
|  Yes  No | Suicidal ideation (thinking about ways to commit suicide) within the past 10 years       |
|  Yes  No | Suicide attempt during the last year                                                     |
|  Yes  No | Schizophrenia                                                                            |
|  Yes  No | Post-Traumatic Stress Disorder (PTSD)                                                    |
|  Yes  No | Other Psychiatric problems (Borderline, Schizoaffective, Hypomania, ADHD)                |
|  Yes  No | Chronic infections syndrome such as HIV, CMV, Epstein Barr                               |
|  Yes  No | Anorexia or bulimia                                                                      |

---

☐ Yes ☐ No    Undergoing acute discontinuation of alcohol, benzodiazepines, barbiturates, or antiepileptic drugs

---

Please list any illnesses that caused you to miss work or have interrupted your life this past year:

1. \_\_\_\_\_ Year: \_\_\_\_\_
2. \_\_\_\_\_ Year: \_\_\_\_\_
3. \_\_\_\_\_ Year: \_\_\_\_\_
4. \_\_\_\_\_ Year: \_\_\_\_\_
5. \_\_\_\_\_ Year: \_\_\_\_\_

Please list any hospitalizations in the past 10 years. If possible, include the year:

1. \_\_\_\_\_ Year: \_\_\_\_\_
2. \_\_\_\_\_ Year: \_\_\_\_\_
3. \_\_\_\_\_ Year: \_\_\_\_\_
4. \_\_\_\_\_ Year: \_\_\_\_\_
5. \_\_\_\_\_ Year: \_\_\_\_\_

Please list any serious injuries or accidents. If possible, include the year:

1. \_\_\_\_\_ Year: \_\_\_\_\_
2. \_\_\_\_\_ Year: \_\_\_\_\_
3. \_\_\_\_\_ Year: \_\_\_\_\_
4. \_\_\_\_\_ Year: \_\_\_\_\_
5. \_\_\_\_\_ Year: \_\_\_\_\_

Please list any surgeries or major procedures. If possible, include the year:

1. \_\_\_\_\_ Year: \_\_\_\_\_
2. \_\_\_\_\_ Year: \_\_\_\_\_
3. \_\_\_\_\_ Year: \_\_\_\_\_
4. \_\_\_\_\_ Year: \_\_\_\_\_
5. \_\_\_\_\_ Year: \_\_\_\_\_

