### **9.3 Exclusion Criteria (assessed study medical provider)**

7. Medical contraindication to the use of Varenicline or Nicotine Patch, or Bupropion (including seizure disorder)
8. Brain abnormality that would increase the patients risk for a seizure (including but not limited to a stroke or brain tumor)
9. Bulimia or anorexia
10. Currently undergoing discontinuation of alcohol or sedative (including benzodiazepines, barbiturates, or antiepileptic drugs)
11. Use of MAO-inhibitor (currently or in the last 14 days)
12. Taking Linezolid or intravenous methylene blue.
13. Significant adverse reaction to bupropion in the past
14. Symptomatic cognitive or emotive disorder such as untreated schizophrenia, severe untreated depression, anxiety.
15. Uncontrolled hypertension (systolic BP >160 mm Hg, diastolic BP >100 mm Hg) or hypotension
16. Chest pain in the last month (unless history indicates a non-cardiac source) or myocardial infarction in the past year
17. Unstable irregular heart rhythm
18. Symptomatic cardiac disorder
19. Moderate renal impairment or mild hepatic impairment (study provider discretion)
20. Current symptomatic lung disorder/disease (including but not limited to COPD, emphysema, and asthma) that requires oxygen
21. Migraine headache occurring more than once per week
22. Unexplained fainting spell within the last month
23. Uncontrolled diabetes (blood sugars >200 more than once per week, suffering from complications or on insulin)
24. Current cancer or treatment of cancer in the past 6 months (except basal or squamous cell skin cancer)
25. History of Tuberculosis or positive PPD
26. Suicidal ideating within the past 12 months or attempted suicide within the last 10 years.
27. Psychiatric hospitalization in the past 12 months
28. Red dye allergy
29. Any other major medical conditions (study provider discretion)

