## **10.7 Study Assessments**

### **10.7.1. Medical History**

Medical history assessments will be completed by each subject as part of standard clinical practice. A Clinical Trials Assistant or other Key Personnel will review this as part of the screening process. Appendix 1 provides an overview of medical history information to be collected and is considered a baseline measure.

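### The Appendix 1 screening form uses look-back windows that contradict exclusions 26 and 27, so a No on its suicide attempt or psychiatric hospitalization item does not clear the exclusion

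*Protocol*

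**What the plan says.** Protocol section 9.3 lists two psychiatric-history exclusions with explicit windows. Exclusion 26 reads "Suicidal ideating within the past 12 months or attempted suicide within the last 10 years". Exclusion 27 reads "Psychiatric hospitalization in the past 12 months". The section heading, "Exclusion Criteria (assessed study medical provider", assigns the judgment to the study medical provider.

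The medical history form in Appendix 1 (Major Medical Conditions) covers the same three histories with yes/no items:

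- "Suicidal ideation (thinking about ways to commit suicide) within the past 10 years"
- "Suicide attempt during the last year"
- "Depression/Anxiety/Bipolar disorder/psychiatric hospitalization in the past 3 months"

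Further down, the same form has a free-text prompt: "Please list any hospitalizations in the past 10 years. If possible, include the year".

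The form belongs to screening. Section 10.1 names the smoking-related medical history questionnaire among the measures collected at the screening examination. Section 10.7.1, which describes Appendix 1, says "A Clinical Trials Assistant or other Key Personnel will review this as part of the screening process".

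**The concern.** None of the three windows on the form agrees with its exclusion, and the 1-year and 10-year suicide windows are interchanged between the two places. That pattern looks more like a transposition than a deliberate choice. A screening form need not repeat every criterion. But where it asks about an excluded history over a shorter period than the exclusion covers, a reassuring answer carries less information than the reader of the form will assume.

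What is at stake is the protocol's own eligibility rule for people who will receive varenicline, nicotine patch or bupropion. The point does not depend on an estimate of drug risk. The varenicline side-effect text in section 5.2 reports slightly more anxiety and mood disorders in people with existing psychiatric conditions, and also reports no increase in suicidal behavior with that drug. The protocol keeps exclusions 26 and 27 regardless, so its screening material should be able to apply them.

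**Working it through.** The plan gives no figure to reproduce. The check sets the printed windows side by side.

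| History | Section 9.3 | Appendix 1 | Difference |
|---|---|---|---|
| Suicide attempt | 10 years (exclusion 26) | 1 year | form shorter by 10 − 1 = 9 years |
| Psychiatric hospitalization | 12 months (exclusion 27) | 3 months, shared box | form shorter by 12 − 3 = 9 months |
| Suicidal ideation | 12 months (exclusion 26) | 10 years | form longer by 10 − 1 = 9 years |

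**Attempt.** A person whose attempt was more than 1 and up to 10 years ago meets exclusion 26 and truthfully answers No to this item. Share of the excluded window that the item does not ask about: 9 / 10 = 90%. A Yes does establish the exclusion.

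**Psychiatric hospitalization.** A person whose stay was between 3 and 12 months ago meets exclusion 27 but falls outside the item. Share of the excluded window not asked about: 9 / 12 = 75%. A Yes is not decisive either, because the same box can be ticked for depression, anxiety or bipolar disorder.

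**Ideation.** The form's 10 years contain the exclusion's 12 months, so a truthful No rules out the ideation part of exclusion 26. A Yes may refer to any time in 10 years, and only the most recent 12 months are excluded. The item cannot tell the two apart.

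**Other places where the gaps might be closed.**

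- PHQ-9 question 9 (exclusion 3, Appendix 16) refers to the past two weeks. For ideation it leaves 2 weeks to 12 months unresolved, and it does not ask about attempts.
- The 10-year ideation item may draw a Yes from someone with an older attempt, but it asks about thoughts, not attempts.
- The hospitalization list spans 10 years but is free text, does not name psychiatric stays, and makes the year optional. An attempt that did not lead to admission would not appear there.
- The form also asks for illnesses that disrupted the past year and has undated boxes for several psychiatric diagnoses. Either could prompt a follow-up question; neither asks about an admission.
- Section 9.3 has the study provider assess these exclusions, and the consent text in section 10 lets medical staff review the medical record. Section 10 also recruits through internet advertisements and pre-screen failures from other studies, so a full health-system record cannot be assumed for everyone.

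Nowhere in the protocol is there a printed question on attempts over 10 years or on psychiatric stays over 12 months.

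**The case against.** The strongest reply is that the form is not the eligibility test. Section 10.7.1 calls it an overview and a baseline measure. Many of its items match no exclusion, and some that do match carry no time window, such as heart attack and fainting. Nothing in the protocol says that a No on the form clears an exclusion. The provider decides, with access to the record. Someone with an older attempt would often have to answer Yes to 10-year ideation, and a psychiatric admission in the past year should appear on the hospitalization list even if undated.

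Much of this stands. It rules out the stronger inference a reader might draw, that people who meet exclusions 26 or 27 will be randomized, or that 90% and 75% of them would be missed. Those percentages are shares of calendar time for single tick-boxes, not of people, and the documents give no count of candidates in the gaps. It also rules out reading the ideation item as a route by which excluded people get through, since that item is wider than its exclusion.

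The reply does not remove the contradiction. Several other items do carry the criterion's own window, including chest pain in the last month, cancer treatment in 6 months and MAO inhibitor use in 14 days. A reviewer can therefore reasonably expect these items to do so too. A provider who relies on the form's dated answers would be misled on two of the three.

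**Conclusion.** The inconsistency is real and the text is wrong as written. Section 9.3 and Appendix 1 give different windows for all three histories. The form is shorter than the exclusion by 9 years for attempts and by 9 months for psychiatric hospitalization, so a truthful No on either does not exclude ineligibility. For ideation the form is longer by 9 years, and the risk there is an unresolved Yes or the wrongful flagging of an eligible person.

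Enrollment of an excluded person is possible, not certain. How likely it is depends on how thoroughly the provider asks and what record is available, which the protocol does not fix. The finding assumes only that the form is used at screening as sections 10.1 and 10.7.1 describe. It concerns eligibility and participant safety; it does not affect the primary analysis or the sample size. The documents do not show which set of windows was intended, and this review takes no position on that.

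**What to change.** Reconcile section 9.3 with Appendix 1. The investigators confirm the intended window for ideation, attempt and psychiatric hospitalization, and each is printed identically in both places. Psychiatric hospitalization gets its own item, apart from depression, anxiety and bipolar disorder.

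For participants already screened, the study provider confirms exclusions 26 and 27 from the medical record or by asking at a scheduled visit or call. Re-reading the completed forms is not enough, because they cannot reveal an attempt or admission that was never asked about.

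The cost is a form correction with the IRB approval that section 14.7 requires for amendments, plus one provider check per participant already screened. No new visit or procedure is needed.

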**Consent:** Interested individuals will be provided with the Study Consent Form (CF), which provides a description of the study. The CTA will review the consent form with the potential participant, read key sections out loud, clarify terms as needed, and answer questions. Ability to read and understand English will be assessed at this time. If unable, the consent process will be discontinued. After reviewing the CF, if the interested individual is interested in participation in the study, they will be asked to sign consent in order to continue screening (completion of exclusion criteria and pregnancy testing). This will include assessment of data collected in EPIC specifically for the Duke Smoking Cessation Program Initial Clinic Visit. The study medical staff (PA or MD) will have access to the potential participant's EPIC record in order to review the Duke Smoking Cessation Program Initial Clinic visit for participant eligibility as well as other pertinent elements of the patient's medical record to ensure their safe inclusion in the study. Individuals who pass Inclusion/Exclusion Criteria will be required to take a urine pregnancy test if they are of child-bearing potential, as defined by the Duke IRB.

| SCHEDULE OF ACTIVITIES                                    |                        |                         |                                  |                               |                                                          |                               |                                     |
|------------------------------------------------------------------|------------------------|-------------------------|----------------------------------|-------------------------------|----------------------------------------------------------|-------------------------------|-------------------------------------|
|                                                                  | Screening Phase | Treatment Phase  |                                  |                               | End of Treatment                                  | Phone Follow up Period | End of Study                 |
|                                                                  | Screening Visit | Enrollment Visit | Medication Response Visit | 2-week post Quit Visit | 12-week Post Quit Visit (Discontinue Medications) | Calls 1-9              | 52-week post quit phone call |

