## 10.1 Screening Examination

The screening examination will take place on the day of the screening visit. Subject data to be collected at the Screening Examination includes the following baseline measures: contact information questionnaire, demographics questionnaire, smoking-related medical history questionnaire, TSCP smoking history questionnaire, recent smoking history questionnaire, medication use and intolerance questionnaire, financial questionnaire, work break questionnaire, cost of smoking questionnaire, general health questionnaire, cancer questionnaire, self-efficacy questions, Fagerstrom Test for Nicotine Dependence (FTND), Mood and Physical Symptoms Scale (MPSS), Patient Health Questionnaire (PHQ-2 as well as PHQ-9 question 9), Generalized Anxiety Disorder-2 (GAD-2), Alcohol Use Disorders Identification Test (AUDIT-C), and the Perceived Stress Test (PSS-4). The subject will also complete a urine pregnancy test if female and of child-bearing potential.

The urine pregnancy test will be conducted by the CTA or other study staff with the appropriate training. Most information except the urine pregnancy test results will be documented in the EMR because these assessments are all part of standard clinical practice within the TSCP. If the screening visit occurs at the CSC, outside of the normal TSCP clinic, all information will be collected on paper forms or in REDCap. If the screening visit occurs at the TSCP during a routine clinic visit, the study Physician or Physician Assistant will review the visit documentation to assess eligibility. In the event of a screen failure, documentation of this will be noted in eResearch. Participants that fail the screening process will receive follow-up from the study physician to ensure the participant has been connected to appropriate clinical care.

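### Appendix 1 reverses the two time windows of exclusion 26, so the only suicide-attempt question does not ask about attempts 1 to 10 years ago

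*Protocol*

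**What the plan says.** Section 9.3, item 26, excludes: "Suicidal ideating within the past 12 months or attempted suicide within the last 10 years". The section heading assigns this criterion to the study medical provider.

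Appendix 1, under Major Medical Conditions, has two yes/no items on the same subject. One reads "Suicidal ideation (thinking about ways to commit suicide) within the past 10 years". The next reads "Suicide attempt during the last year".

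Appendix 1 is part of screening. Section 10.1 lists the "smoking-related medical history questionnaire, TSCP smoking history questionnaire" among the measures taken at the screening examination. Section 10.7.1 says of the medical history: "A Clinical Trials Assistant or other Key Personnel will review this as part of the screening process".

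The consent text in section 10 also gives the study PA or MD access to the electronic record, including pertinent parts of the "medical record to ensure their safe inclusion in the study".

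**The concern.** The criterion and the form use the same two durations, attached to opposite events. For ideation the form is wider than the rule, so it misses nobody, although a Yes does not separate the excluded last 12 months from the years before. For attempts the form is narrower than the rule, which is the unsafe direction.

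At stake is a participant-safety exclusion in a trial of varenicline and bupropion. Section 11.1.1 names no adverse events of special interest, so for suicidality history the entry criterion is the main explicit protection. If staff rely on the form as printed, someone whom item 26 excludes could be enrolled without ever being asked directly about an attempt.

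**Working it through.** The protocol gives no figure to reproduce here. The check sets each criterion beside the form item that should capture it.

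| Subject | Criterion | Form | Difference |
|---|---|---|---|
| Suicide attempt | 10 years (9.3, item 26) | 1 year (Appendix 1) | 120 − 12 = 108 months not asked; 108/120 = 90% |
| Suicidal ideation | 12 months (9.3, item 26) | 10 years (Appendix 1) | 120/12 = 10 times wider; none missed |
| Psychiatric admission | 12 months (9.3, item 27) | 3 months, in one item with depression, anxiety and bipolar disorder (Appendix 1) | 12 − 3 = 9 months not covered by the yes/no item |
| Illicit drug use | 1 month (9.2, item 2) | 1 week (Appendix 2) or 1 year (Appendix 10) | about 30 days against 7 or 365; neither matches |
| AUDIT-C positive | 5 women, 6 men (9.2, item 1) | 3 women, 4 men (10.7.3 and Appendix 9) | 2 points per sex; scores 3–4 (women) and 4–5 (men) are classed differently |

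**Is there another question on attempts?** No. Question 9 of the PHQ-9 (Appendix 16) is also collected at screening, and any score above 0 is exclusionary under 9.2, item 3. It asks about thoughts over the past two weeks, not about past attempts.

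**Is the form just a loose history with no link to the criteria?** Not entirely. Where Appendix 1 gives an explicit window for other exclusions, the window agrees with 9.3:

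- "Chest pains related to the heart in the last month" agrees with item 16 (1 month).
- "Current cancer or treatment for cancer in the past 6 months" agrees with item 24 (6 months), although the form omits the skin-cancer exception.
- The MAO-inhibitor question agrees with item 11 (14 days).

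The form asks about heart attack and unexplained fainting with no window at all, so those two items can only over-capture. The attempt and psychiatric-admission items are narrower than their criteria.

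**Direction of the lesser mismatches.**

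- The psychiatric-admission gap is largely covered by the form's free-text list of hospitalizations over 10 years, although the year is requested only where possible.
- Appendix 10's one-year drug question would include everyone who used in the last month, but section 10.1 does not list it among the screening measures. Appendix 2's one-week question would miss use 8 to 30 days earlier.
- The AUDIT-C conflict lets no excluded person through. Both texts send a positive screen to a clinician, so it changes only who is referred.

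**The case against.** The strongest reply is that the swap partly repairs itself. The ideation item just above the attempt item covers 10 years, the same window as the attempt exclusion. Most people who attempted suicide in that period would have to answer Yes to it. In addition, item 26 is a judgement by the medical provider and not a form score, the provider can read the medical record, and the free-text lists of hospitalizations and of serious injuries may reveal an attempt. Appendix 1 is also a general clinical history and does not mirror section 9.3 line by line.

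Much of this stands, and it is why the point is a risk and not a demonstrated failure. It does not close the gap, for four reasons:

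- A Yes on 10-year ideation does not establish whether an attempt occurred.
- The hospitalization list catches only attempts that led to admission and can be recognised from free text.
- When screening takes place at a routine clinic visit, section 10.1 has the physician or PA review that visit's documentation to assess eligibility, so a provider who relies on it inherits the form's gap.
- Participants recruited through internet advertisements may have little institutional record to review. This is an inference; the protocol does not say so.

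The point that AUDIT-C cannot be settled by changing a form alone is correct. The lower cut-off also stands in section 10.7.3, so the body text must change too.

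**Conclusion.** The concern holds. Exclusion 26 and the form used to screen for it contradict each other, and the protocol's only attempt question omits 9 of the 10 excluded years. The consequence is a possible missed safety exclusion, reduced by provider assessment, record review and the 10-year ideation item.

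How many of the planned 300 participants could be affected cannot be calculated, because the protocol gives no prevalence of past attempts. No endpoint, comparison, sample size or analysis changes. The conclusion assumes that the form is used as printed and that section 9.3 states the intended rule. The point should be fixed, but it does not call the design into question.

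**What to change.** In Appendix 1, ask about a suicide attempt over the last 10 years and suicidal ideation over the past 12 months. Make psychiatric hospitalization over the past 12 months an item of its own. Add a screening question on illicit drug use in the last month. Choose one AUDIT-C cut-off pair and use it in section 9.2, section 10.7.3 and Appendix 9.

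For anyone already enrolled whose record does not document attempt history over 10 years, check that single point. A full re-screen is not needed.

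The cost is a form revision, a short amendment and the one-point history check where documentation is lacking. There may be some additional screen failures, but the protocol gives no basis for estimating how many.
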